### Strategies to improve adherence to intervention/comparator {15c}

Educational settings allocated to receive training and deliver II will receive support from a SaLT during their time in the trial. Training and resources will be provided online, and interventionists will be able to revisit these as required.

Interventionists, and parents/carers if they choose to deliver II at home, will be asked to complete a session record log each day during the intervention period to record key aspects of implementation. Whilst the trial team encourages the completion of session logs, it is anticipated that some settings or parent/carers may not action this request or may do so inconsistently. No attempts will be made to backfill any missing data as this would rely heavily on recall over a long period. Speech and language therapists appointed by the trial team to support the settings will meet with setting staff and parent/carers weekly for the first 4 weeks and then monthly thereafter to provide support and encourage adherence.

### Concomitant care permitted or prohibited during the trial {15d}

As II is complementary to the usual package of support and education received by children and young people with PMLD, no concomitant care will be prohibited during the course of the trial.

### Ancillary and post-trial care {34}

All participants will continue to receive their usual care and education following the trial. Settings that received the II training are able to continue delivering II at their discretion. Settings that are allocated to continue with care and education as usual will have the option to receive II training and support from a SaLT at the end of their trial period (52 weeks post-randomisation).

II is already widely used within educational settings and we do not anticipate any harm will come to trial participants as a consequence of receipt.

### Outcomes {16}

Data will be collected at baseline, 32- and 52–weeks post-randomisation from staff at educational settings and parents/carers.

#### Primary outcome

The primary outcome is the Communication Complexity Scale (CCS) [11–13] completed at 32 weeks post-randomisation. The CCS was developed to describe and measure the development of pre-intentional and intentional communication in individuals with developmental disabilities and minimal verbal skills. It has demonstrated good reliability and validity in children with intellectual and developmental disabilities [12]. The CCS consists of a 12-point scale and covers three levels of early communication (pre-intentional, intentional non-symbolic and intentional symbolic), with higher scores reflecting more complex communication. Lower scores describe no response (0), alerting (1) or pre-intentional communication acts (2–5), scores of 6–10 are for intentional non-symbolic communication acts and scores of 11–12 are for intentional symbolic communication acts (e.g. using speech, signs or symbols; 11).

In the trial, the CCS will be used to score naturalistic sessions [14]. At each time point, the associated teacher will be asked to video themselves and the participating child or young person interacting for approximately 10 min following guidance provided by the trial team. Video recordings will be scored using the CCS by members of the research team who are blind to allocation. In line with training and guidance from the CCS developers, each video will be split into 30-s intervals, and each interval will be allocated a score of 0–12, i.e. the score for the highest scoring communication act within that interval. For scores of 6–12 (i.e. intentional communication), a function score will be allocated according to whether the function of the communication act was for ‘behaviour regulation’ (i.e. to bring about a specific result by requesting or protesting) or ‘joint attention’ (i.e. to direct a communication partner’s attention for social commenting; 11). An ‘optimal score’ will be calculated at each time point by averaging the three highest CCS scores [11]. The optimal score at 32 weeks post-randomisation will be the primary outcome and the optimal score at 52 weeks post-randomisation will be a secondary outcome.

#### Secondary outcomes

Secondary outcomes will also be collected at baseline, 32- and 52- weeks post-randomisation. These are outlined below, grouped by respondent.

Parent questionnaires:Quality of Life–Profound Multiple Disabilities (QOL-PMD): measuring quality of life [15]: mean difference in total scores between groups at 32 and 52 weeks adjusting for baselineShort Warwick-Edinburgh Mental Well-being Scale (SWEMWBS): measuring parental wellbeing [16]: mean difference in total scores between groups at 32 and 52 weeks adjusting for baselineMood, Interest and Pleasure Questionnaire—Short Form (MIPQ-S) [17]: mean difference in total scores between groups at 32 and 52 weeks adjusting for baseline

Teacher questionnaires:Modified Routes for Learning [18]: mean difference in total scores between groups at 32 and 52 weeks adjusting for baselineEducation Health and Care Plan (EHCP) Changes: estimated treatment effects at 32- and 52–weeks and overall will be presented as an odds ratioBehaviour Problems Inventory-Short Form (BPI-S) [19]: mean difference in total scores between groups at 32 and 52 weeks adjusting for baseline

#### Health economics outcomes

The following outcome measures will be collected for the purpose of the economic evaluation. How these will be analysed is detailed under item 27a.

Parent questionnaires:Child Health Utility-9D (CHU-9D) proxy version: measuring quality of life [20]EQ-5D-Y proxy version: measuring quality of life [21].The Carer Experience Scale: measuring parental quality of life [21]Bespoke Resource Use Questionnaire: measuring personal, healthcare, social, educational and societal resource use [20]

Teacher questionnaires:EQ-5D-Y proxy version: measuring quality of life [21]Bespoke Resource Use Questionnaire [22]: measuring resource use within the educational setting

#### Other collected variables

At baseline, teachers will be asked whether each child/young person has a sight impairment, hearing impairment, epilepsy diagnosis, whether epilepsy is controlled, whether the child or young person has a diagnosis of autism, and whether the child/young person receives their nutrition orally. At baseline, parents/carers will be asked to report the child/young person’s biological sex, ethnicity and living arrangements, as well as their own gender, ethnicity and relationship status.

### Harms {17}

Given the nature of the intervention being evaluated, no adverse events (AE) or serious adverse events (SAE) that are unexpected and related are anticipated. However, as the intervention sessions will be novel for the children and young people, and they may intrude on some children’s existing routines, this might cause distress for some children/young people with PMLD.

We will take a non-systematic approach to adverse event approaching, rather we will ask SaLTs, interventionists based at the educational settings and parents/carers in both arms of the trial to report if they have a concern about a participating child or young person or they experience an incident, event, negative change (e.g. to their communication or behaviour) or out of character distress that may be related to taking part in the INTERACT trial.

Following consultation with our research advisory group and drawing on the trial team’s clinical knowledge, we will collect data regarding specific adverse events as follows:New or worsening behaviour that challengesExhibited a level of distress that is out of characterReduced levels of communication.Injured at home or at setting.Hospitalised unexpectedly for any reason or had a planned hospital stay unexpectedly lengthened.Negative changes to sleep patternsReduced access to respite due to changes in behaviour.Moved to a different educational setting unexpectedly due to additional needs.New involvement from Child and Adolescent Mental Health Services.Other concerns (please specify)

Participating SaLTs, interventionists and parent/carers will be provided with the list above and asked to report any occurrences by telephone to York Trials Unit using a dedicated trial telephone number. The trial team will then complete an adverse event form and follow up as appropriate.

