### Recruitment {20}

The study aims to recruit 66 educational settings and 330 children/young people with PMLD from Great Britain. Recruitment will take place in three waves during 2023, 2024 and 2025. Data will be collected from a nominated teacher and a nominated parent/carer for each participating child/young person. For those allocated to receive the intervention, data will also be collected from the child/young person’s main communication partner (referred to as the interventionist). Recruitment will be both targeted and opportunistic.

Educational settings serving children and young people with PMLD across Great Britain will be contacted by email with a recruitment flyer containing basic information about the trial and a link to the trial website.

We will also publicise the study on social media platforms, such as X, Facebook and LinkedIn. The Council for Disabled Children and PAMIS may also promote the materials through their connections, webpages and newsletters.

Interested parties will be required to complete an online expression of interest form which acts as a screening tool to ensure settings meet the required inclusion criteria. Those that express an interest in participating and are confirmed eligible will be sent full details about the study, more specific information about the population characteristics, as well as a memorandum of understanding (MOU) and Data Sharing Agreement (DSA) to complete.

Following the receipt of a valid MOU and DSA, settings will be provided with recruitment packs to distribute to families. Families will be given the option of completing an online consent form or a paper copy. Paper copies will be securely sent from the educational setting to York Trials Unit for processing.

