#### Adverse events

Adverse events will be summarised descriptively. The frequency of each of the pre-specified adverse events will be reported by trial arm.

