## Abbreviations

AE: Adverse event
BPI-S: Behaviour Problems Inventory-Short Form
CCS: Communication Complexity Scale
CES: Carer Experience Scale
CHU-9D: Child Health Utility-9D
CI: Chief investigator
CONSORT: Consolidated Standards Of Reporting Trials
DMC: Data Monitoring Committee
DSA: Data Sharing Agreement
EHCP: Education Health Care Plan
EQ-5D-Y: European Quality of Life-5 Dimension-Youth
GP: General practitioner
HEAP: Health economics analysis plan
HTA: Health Technology Assessment
ICER: Incremental cost-effectiveness ratio
INCLUDE: INCLUDE is an initiative from the UK’s National Institute for Health Research (NIHR) that aims to improve trial delivery for under-served groups
Interventionist: A member of setting staff or parent/carer who will deliver the intervention
II: Intensive Interaction
ITT: Intention to treat
MOU: Memorandum of understanding
NASEN: National Association for Special Educational Needs
NHS: National Health Service
NICE: National Institute for Health and Care Excellence
NIHR: National Institute for Health and Care Research
PAMIS: Promoting A More Inclusive Society
PIS: Participant Information Sheet
PMLD: Profound and multiple learning disabilities
PPIE: Patient and Public Involvement and Engagement
PSS: Personal Social Services
QALY: Quality-adjusted life years
QOL-PMD: Quality of Life-Profound Multiple Disabilities Questionnaire
RAG: Research Advisory Group
RCT: Randomised controlled trial
SAE: Serious adverse events
SaLT(s): Speech and language therapist(s)
SAP: Statistical analysis plan
SENCO(s): Special Educational Needs Co-ordinator(s)
SEND: Special Educational Needs and Disabilities
SOP: Standard Operating Procedure
SWEMWBS: Short Warwick-Edinburgh Mental Well-being Scale
TA: Teaching assistant
TMG: Trial Management Group
TSC: Trial Steering Committee
UK: United Kingdom
YTU: York Trials Unit

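### Adverse events are telephoned in by three kinds of reporter, of whom only parents/carers clearly exist in both arms, so the by-arm frequencies mix chance of being reported with harm

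*Protocol article*

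**What the plan says.** **Collection.** Harms {17} declares the method openly: "We will take a non-systematic approach to adverse event approaching". The people asked are "SaLTs, interventionists based at the educational settings and parents/carers in both arms of the trial to report if they have a concern". It then gives a list of nine specific events plus an open category, and says: "Participating SaLTs, interventionists and parent/carers will be provided with the list above and asked to report any occurrences by telephone".

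**Threshold.** The general request covers concerns, incidents, negative changes or "out of character distress that may be related to taking part in the INTERACT trial". The later sentence, about the list, asks for any occurrence with no condition on relatedness.

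**Who the reporters are.** The Abbreviations define an interventionist as "A member of setting staff or parent/carer who will deliver the intervention". Recruitment {20} adds: "For those allocated to receive the intervention, data will also be collected from" the main communication partner, meaning the interventionist. Implementation {23} has SaLTs identified after randomisation, for settings allocated to II. Under section {15c}, SaLTs appointed by the trial team "will meet with setting staff and parent/carers weekly for the first 4 weeks and then monthly thereafter". Under Comparator, control settings receive training and support only once the 52-week follow-up is done. The Abstract, by contrast, gives every participant an interventionist.

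**Reporting.** The statistical section on adverse events is descriptive: "The frequency of each of the pre-specified adverse events will be reported by trial arm".

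**The concern.** A frequency table by arm can be read across only if an event has about the same chance of entering it in each arm. Here two of the three named channels depend on II being delivered, and families in the intervention arm have scheduled SaLT contact that control families lack. Section {24a} confirms that parents and setting staff know the allocation. A control family whose child's care has not changed has less reason to think that an event might be related to the trial.

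What is at stake is how the harms table is read. An excess in the intervention arm could be harm or could be fuller reporting, and the table cannot separate the two. Equally, a real excess of distress or injury could be dismissed as over-reporting. The protocol itself expects that some children may be distressed, and these children cannot report for themselves.

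**Working it through.** The plan gives no adverse event rate and no reporting probability, so there is no figure of its own to reproduce. The check has two parts.

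**1. Reporters by arm, from the protocol's text**

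| Reporter | Intervention arm | Control arm before week 52 |
|---|---|---|
| Parent/carer | Yes, with SaLT meetings | Yes, without them |
| Setting interventionist | Yes | None by definition (Abbreviations) and no data collection (Recruitment {20}); the Abstract points the other way |
| Trial SaLT | Yes, weekly then monthly contact | None shown; an in-house SaLT may exist, but nothing gives that person a trial role |
| Nominated teacher | Not named as a reporter in that role | Not named as a reporter in that role |

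So the count of reporter types is up to three against one.

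**2. What unequal capture could do (illustration)**

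Assumptions, none of them from the protocol: equal true risk in both arms; each reporter telephones in an event with probability d; reporters act independently; an event reported twice is counted once. With k reporters the chance of capture is 1 − (1 − d)^k. The apparent ratio against one reporter is [1 − (1 − d)^k] / d.

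| d | k = 3 against 1 | k = 2 against 1 |
|---|---|---|
| 0.1 | 0.271 / 0.1 = 2.71 | 0.19 / 0.1 = 1.90 |
| 0.3 | 0.657 / 0.3 = 2.19 | 0.51 / 0.3 = 1.70 |
| 0.5 | 0.875 / 0.5 = 1.75 | 0.75 / 0.5 = 1.50 |
| 0.7 | 0.973 / 0.7 = 1.39 | 0.91 / 0.7 = 1.30 |
| 0.9 | 0.999 / 0.9 = 1.11 | 0.99 / 0.9 = 1.10 |

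With the same reporters and prompts in both arms the ratio is 1.00 for any d.

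In counts: 330 participants allocated 1:1 by setting give about 165 per arm. At an assumed true risk of 20%, each arm has 0.20 × 165 = 33 events. With d = 0.3, the intervention arm records 33 × 0.657 = 21.7 and the control arm 33 × 0.3 = 9.9.

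Independence is generous to the effect. SaLTs meet the same staff and parents, so their reports would overlap and the ratio would fall. Different prompting or a different threshold by arm is not in the formula and could raise it.

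**The case against.** - **The table is descriptive.** This stands. No test, effect estimate or safety objective is planned. A reader might infer that the protocol plans a formal safety comparison; it does not. Frequencies set side by side by arm will still be compared, and no caveat is stated.
- **The list carries no relatedness filter.** This stands in part. Reporters are asked for any occurrence of the listed events, and the hospital item covers any reason. A reader might infer that unrelated events are excluded; the text does not say so. It gives two thresholds in one section, and they need reconciling.
- **The section says both arms, and the Abstract gives each participant an interventionist.** If an interventionist were nominated in control settings too, the gap would narrow. That reading conflicts with Recruitment {20} and the Abbreviations, and it would not remove the difference in SaLT contact.
- **Other data exist in both arms.** This is a real mitigation. The blinded CCS coding, the teacher-reported BPI-S and the parent-reported MIPQ-S cover communication, behaviour and mood. A reader might infer that the trial cannot detect harm at all; these measures show otherwise. They do not record injury, sleep change, lost respite, a move of setting or new mental health service involvement as events.
- **The direction is not certain.** This stands. Unblinded staff who deliver II might under-report. An excess in the intervention arm is likely, not assured.

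**Conclusion.** The point holds for the by-arm adverse event table. As written, the frequencies combine any true difference with a difference in who can report, how often they are in contact with the trial, and which threshold they apply. The bias probably runs towards more recorded events in the intervention arm.

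Its size is unknown. The range of 1.1 to 2.7 rests wholly on assumed reporting probabilities of 0.9 to 0.1, independence, and three reporters against one. With two against one it is 1.1 to 1.9.

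The primary outcome, the economic analysis and the follow-up of individual safety reports are unaffected. The harms most exposed are those with no parallel outcome measure in both arms.

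**What to change.** 1. **All waves, at analysis.** Base the by-arm frequencies on parent/carer reports, the one named reporter type clearly present in both arms. Show SaLT and interventionist reports separately by source, as a listing, and state that they are not comparable between arms. This needs only that the source of each report is known. It removes the difference in reporter types, but not the extra SaLT contact of intervention-arm parents, which should be stated as a limitation.
2. **Protocol text.** State one threshold for the listed events: any occurrence, regardless of suspected relatedness. Name the nominated teacher as a reporter in both arms. Reconcile the Abstract and Harms {17} with Recruitment {20} and the Abbreviations on who is an interventionist in control settings.
3. **Follow-ups still to come.** Add the existing list as yes/no items to the teacher and parent/carer questionnaires used in both arms.

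**Cost.** An amendment, about ten tick-box items and slight respondent burden. Recall would span several months, a weakness the protocol itself recognises when it declines to backfill session logs. Randomisation began in December 2023, recruitment was due to end in December 2025, and last follow-ups are due in December 2026. The items would therefore reach only the later wave or waves. They should supplement the existing reports, because relying on them alone would discard the earlier waves' data.

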### Participant timeline {18}

Participants will be enrolled in the study and the baseline assessment completed in the autumn term (September to December). The intervention will be delivered during spring and summer terms (January to May). Data will be collected 32 weeks post-randomisation (June–July) and 52 weeks post-randomisation (November–December).

### Sample size {19}

The primary outcome is the CCS at 32 weeks. A study utilising the CCS for communication skills of children with autism spectrum disorder who were minimally verbal [13] indicated that a 1-point increase in scores is a minimal clinically important difference (MCID). Assuming a MCID of one point on the CCS [13], a standard deviation of 2.08 [12], 90% power, 5% alpha, 20% loss to follow-up at the child/young person level, 10% drop out at the educational setting level, ICC = 0.09 (calculated from a similar trial published by the trial team, [22] and an average cluster size of 5, we would need to randomise 66 educational settings (330 children and young people). Sample size calculations were conducted in Stata v17 using the command clustersampsi. The Stata code used to determine the number of educational settings is given as follows:clustersampsi, mu1(0) mu2(1) sd1(2.08) sd2(2.08) m(4) rho(0.09) beta(0.9)with further adjustment to the number of educational settings to allow for up to 10% attrition.

### Recruitment {20}

The study aims to recruit 66 educational settings and 330 children/young people with PMLD from Great Britain. Recruitment will take place in three waves during 2023, 2024 and 2025. Data will be collected from a nominated teacher and a nominated parent/carer for each participating child/young person. For those allocated to receive the intervention, data will also be collected from the child/young person’s main communication partner (referred to as the interventionist). Recruitment will be both targeted and opportunistic.

Educational settings serving children and young people with PMLD across Great Britain will be contacted by email with a recruitment flyer containing basic information about the trial and a link to the trial website.

We will also publicise the study on social media platforms, such as X, Facebook and LinkedIn. The Council for Disabled Children and PAMIS may also promote the materials through their connections, webpages and newsletters.

Interested parties will be required to complete an online expression of interest form which acts as a screening tool to ensure settings meet the required inclusion criteria. Those that express an interest in participating and are confirmed eligible will be sent full details about the study, more specific information about the population characteristics, as well as a memorandum of understanding (MOU) and Data Sharing Agreement (DSA) to complete.

Following the receipt of a valid MOU and DSA, settings will be provided with recruitment packs to distribute to families. Families will be given the option of completing an online consent form or a paper copy. Paper copies will be securely sent from the educational setting to York Trials Unit for processing.

#### Recruitment to the process evaluation

As part of the process evaluation, interviews will be conducted with key stakeholders responsible for delivering the intervention, including SaLTs, educational practitioners and the parents/carers of participating children. The research team will work closely with staff in educational settings to ensure that a diverse sample of parents/carers and staff involved in delivering the intervention is selected according to the following criteria: staff group (education practitioners, SaLTs), educational setting size and type (SEND, mainstream educational settings with SEND units), geographical location, PMLD, and child’s age, gender and ethnicity. The preparatory work undertaken to identify ‘target educational settings’ will be crucial to our sampling by illustrating the sites where we may wish to focus our efforts to achieve this diversity. SaLTs, educational practitioners and parents/carers will be invited by the qualitative research team via email/phone call to take part in a qualitative interview including a copy of the Participant Information Sheet and will be sent an online consent form if they wish to participate.

